#### Clinical measures

The following measures will be administered at T0, T1 and T2:Depressive symptom severity*.* The PHQ-9 will be completed during the consent appointment to determine depressive symptom severity. The PHQ-9 is widely used in primary health care research [36]. It is a 9-item self-report measure of depression severity used with good sensitivity and specificity. Items are rated on a 4-point scale. Scores 5–9 are considered mild, 10–14 moderate, 15–19 moderately severe and 20+ severe [37].Generalised anxiety will be measured with the Generalised Anxiety Disorder-7 (GAD-7) [38], a 7-item measure of generalised anxiety. Items are rated on a 4-point scale, and the measure has excellent psychometric properties [39].Wellbeing will be measured with the short version of the Warwick Edinburgh Mental Well-being Scale [40], which consists of seven questions rated on a 5-point scale designed to measure wellbeing. The scale has good psychometric properties and is used widely [41, 42].

#### Potential mechanisms

The following measures will be administered at T0, T1 and T2:Connectedness to nature will be measured using the connectedness to nature scale [43], which consists of 15 questions rated on a 5-point scale validated scale for measuring connectedness to nature. This will be administered at time 0, time 1 and time 2.Loneliness will be measured using three questions rated on a 3-point scale and one question on a 5-point scale, and the three-question survey has good psychometric properties [44] and is used widely in conjunction with the final question [45].Self-compassion will be measured using the 20 question Sussex-Oxford Compassion for Self-Scale (SOCS-S) that is rated on a 5-point scale [46] The scale has excellent psychometric properties.Mindfulness will be measured using the 15-item version of the Five-Facet Mindfulness Questionnaire [47]. This has excellent psychometric properties.

The PPI group was consulted on the use of these measures and the most appropriate formats. As a result, surveys will be offered as an online form available via e-mailed links, surveys completed by phone with the participant or in paper version, whichever the participant finds most useful and acceptable.

#### Health economic measures

The following health economics outcomes and measures will be collected at T0, T1 and T2.

*Health-related quality of life (HRQoL)*: HRQoL will be measured using the following:The EQ-5D-5L [48] — This is a well-validated, generic, preference-based measure of HRQoL in adult populations, widely used across disease areas, including mental health. It includes five dimensions covering domains of everyday life, i.e. mobility, self-care, usual activities, pain/discomfort and anxiety/depression, each with five-ordered levels of response. It is designed to estimate quality-adjusted life years (QALYs) and recommended by the UK National Institute for Health and Care Excellence (NICE) for use in economic evaluations for health technology assessment [49].The ReQoL-10 (Recovering Quality of Life-10) [50] — This is a specific measure of HRQoL for people aged 16 years old or more experiencing a wide range of mental health difficulties, including anxiety and depression. The recently developed valuation of the ReQoL-10, i.e. the ReQoL-Utility Index (UI) [51], can be used for estimating QALYs. It will be used in this feasibility study as a sensitivity measure.

*Resource use*: A societal perspective for resource use data collection will be adopted as mental health consequences/costs go beyond the health and social care sectors, e.g. including the labour market. The following questionnaires will be tailored to the target population with input from the PPI group:Client Service Receipt Inventory (CSRI) [52] form: A modified version of the CSRI will be used to collect information on participants’ type and intensity of usual care for depression for the duration of the study, as applicable, use of other health and social care resources (e.g. GP visits, medications) and time/cost of travelling to/from treatment locations. This has good agreement with case records [53]. Participants will also be provided with “ad hoc” designed diaries to help recalling of resources used between assessment points.Institute of Medical Technology Assessment (i-MTA) Productivity Cost Questionnaire (iPCQ) [54]: An adapted version of the iPCQ will be used to capture the impact of mental health on employment in a paid job and on unpaid work (e.g. household chores).“Ad hoc” form/logs: These bespoke form/logs will capture the relevant setup and on-going resources necessary to offer the outdoor swimming courses (e.g. insurance; lifesaving equipment). They will include specific logs for swimming coaches and their supervisors (for recording time spent on training and preparation/delivery of the outdoor swimming course) and logs for link workers (to record time spent advising participants).

#### Intervention evaluation measures and tools

A qualitative component of the study will explore the available evidence to help identify facilitators and barriers to participation in both arms of the trial. The following tools have been developed to support qualitative data collection:A questionnaire for people who choose not to participateA semi-structured focus group discussion schedule for social prescribersA questionnaire and semi-structured interview schedule for participants who do not complete the studyA semi-structured focus-group discussion schedule for swim coachesAn evaluation questionnaire, semi-structured focus-group discussion and semi-structured interview schedule for participants in the intervention armAn evaluation questionnaire, semi-structured focus group discussion and semi-structured interview schedule for participants in the control arm

### Procedure

See Fig. 1 for the SPIRIT [55] schedule of enrolment, interventions and assessments. Participants with mild to moderate symptoms of depression will be sought through social prescribing services and self-referral. The study will be advertised by social prescribers and elsewhere through social media. Informed consent will be obtained from each participant by the recruitment team (HM, AB, RC and AJ). Potential participants will be given a copy of the study participant information sheet and will have the opportunity to discuss the study with the research assistant (RA) by phone or video call before signing the consent form (a copy of which can be obtained from the corresponding author). Written and verbal consent will be received at least 24 h after participants are given the participant information sheet.

To assess the risk at entry to the trial, initial information will be gathered from self-reported online health history questionnaires about the participant’s medical history. The research assistant will also perform the PHQ-9 at the consenting phone call. The health history questionnaire and PHQ-9 will be assessed by the medical team RC and AB (both psychiatrists) who will evaluate the risk. Following this, those deemed at high risk will be contacted by the medical team via a phone call, and those deemed as low risk or where further information is required will be contacted by the research assistant or other members of the research team either by phone or email and answers discussed with the medical team if necessary. During the study, if a concern is raised by the participant, swim coaches or a study team member the medical team will contact those involved and recommend the actions to be taken, if any.

Once the participant has consented to participate in the trial, the participant will complete the full set of baseline measures. Measures will be completed online, on paper or with an RA present by telephone depending on participant preference. Participants who do not meet eligibility criteria at the baseline assessment will be referred to social prescribers to be offered alternative activities.

At the end of the baseline assessment, eligible participants will be randomised to either the swim and usual care or usual care only arm. Eligible participants will be randomly allocated using the Sealed Envelope online service [56]. The study statistician will use Sealed Envelope to set up and test the randomisation procedure, incorporating stratification by site using random permuted blocks and 1:1 allocation. The statistician will not have any further involvement in the randomisation process. One of the Co-CI’s (H. M.) will randomise participants by completing the online form with participant’s details. This will immediately show whether the participant is assigned to the swim course intervention plus usual care or usual care only arm. Participants assigned to the intervention will be given details of the swim courses and, where possible, support from social prescribers to attend the sessions. Participants will continue with their usual care and complete the surveys at T0, T1 and T2, with the intervention group participating in 8 outdoor swimming sessions. The quantitative data analysis team (AMBJ and MV) will remain blinded until the quantitative data analysis is complete. The RA-supporting participants to complete measures will remain blinded until all quantitative data is collected.

The outdoor swim courses are led by experienced qualified outdoor swimming coaches who have mental health awareness training. Swim coaches will contact participants before the first session to ensure they know what to bring with them and answer any questions. The swim coaches will contact participants 24 h before each session to support their attendance and provide any additional information e.g. a change of plan due to inclement weather. If possible, social prescribers will support participants to their first session. This mirrors the usual way in which social prescribers provide support for clients attending new activities.

Participants will complete further measures online (with a postal option) at the post intervention time point (T1), or equivalent time point if they are in the usual care group and at 8-week follow up (T2). Participants will have the option to choose whether to complete the T1 and T2 measures with an RA present by telephone (who will be blind to group allocation) or on their own. In the event that an RA is required to be present during T1 and T2 assessments and becomes unblinded, the assessment will be completed by another blinded team member. However, participants will be asked not to reveal which arm of the study they were randomised to. Where T1 and T2 assessments are not completed, participants will be contacted at weekly intervals for up to 1 month to remind them to complete these assessments, unless participants have discontinued from the study.

The qualitative data will be collected using questionnaires, focus groups and interviews. A questionnaire will be sent to those declining to participate and a questionnaire and an invitation to participate in an interview to those who do not remain in the study. The questions are designed to understand any barriers they encountered and to determine any changes that could be made to improve recruitment and retention in the definitive trial. Following completion of recruitment and the swim courses, the social prescribers and swim coaches will all be invited to participate in focus groups to explore their understanding of any facilitators and barriers. Finally, at the end of the follow-up period (T2), all study participants will be sent an evaluation form. This will provide an opportunity to feedback about their experiences of the study; the intervention group evaluation form will also ask about their experience of being on the swim course. They will also all be invited to attend a focus group, to gather further detailed information about their experiences. Six focus-group sessions will be offered: one for participants in the intervention arm and one for controls in each location. Additionally, participants will be invited for an interview if further in-depth exploration of their experience would be useful. Information gathering will be purposive, and analysis will be undertaken alongside data collection and inform when sufficient data has been achieved. Questions were added to the evaluation form and semi-structured interview schedule by the trial lived experience and PPI team to improve the understanding of the experience of the study from a participant perspective.

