## Methods/design

### Design and sample size

This is a parallel-group, pragmatic superiority feasibility RCT with 1:1 allocation to an 8-session outdoor swimming course plus usual care or usual care only. Using random permuted blocks, we will randomly allocate 88 people meeting eligibility criteria to receive the eight 1-h sessions of a swim course provided by trained and experienced outdoor swim coaches, on top of usual care or usual care only. Stratification is by location (three sites in England). Participants will complete measures at baseline (T0), post swim course or the equivalent time point for the usual care only group (T1) and again after a further 8 weeks (T2) for follow-up (see Fig. 1).

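### The co-chief investigator who randomises and sees each allocation also belongs to the consent team, which allows better-than-chance guesses of the next arm while recruitment continues

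*Protocol article*

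**What the plan says.** All of the role assignments are in the Procedure section of the protocol article.

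- Consent: "Informed consent will be obtained from each participant by the recruitment team". Four sets of initials follow.
- Sequence: the study statistician sets up a third-party online service, "incorporating stratification by site using random permuted blocks and 1:1 allocation", and then steps back: "The statistician will not have any further involvement in the randomisation process".
- Randomisation: one co-chief investigator "will randomise participants by completing the online form". The initials given match one of the four consent-takers.
- Disclosure: "This will immediately show whether the participant is assigned to the swim course intervention plus usual care or usual care only arm".
- Order: randomisation comes only after consent, the eligibility check and the baseline measures.
- Blinding: promised for the quantitative analysis team and for the research assistant who helps with measures. The co-chief investigator who randomises is not covered.

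Design and sample size confirms permuted blocks and three sites as strata. Block size is not given, nor whether it is fixed or varied.

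**The concern.** Blocks force the arms back to balance within each site, so a site's past allocations carry information about the next one. A central service hides the next entry but not what follows from the history. Here one recruiter accumulates that history for every site and can go on taking consent.

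The person concerned could, without meaning to, encourage a keen applicant more warmly, or bring one forward, when the swim arm looks due. There is some room for discretion: the exclusion for other severe mental illness has no threshold, and the Procedure section lets members of the research team other than the research assistant follow up low-risk or unclear cases.

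Two progression quantities are exposed. Planned data analysis makes a full trial depend on whether the 95% interval for the PHQ-9 difference includes a 1.7-point benefit. Criteria for success requires 80% to attend four or more swim sessions. PHQ-9 is self-reported by people who know their arm. Keener people in the swim arm would tend to flatter both.

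**Working it through.** **Number of allocations.** Design and sample size gives 35 per arm and 20% drop-out. 35 / (1 − 0.20) = 43.75, rounded up to 44; 2 × 44 = 88. The stated total is reproduced. Spread over three sites, this is about 29 per site (29, 29 and 30 assumed).

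**Role overlap.** The consent sentence and the randomisation sentence share one set of initials. No sentence takes that person out of consent or eligibility once randomisation has begun.

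**How well the next arm can be guessed.** All block sizes below are assumptions. The best guess is the arm that is behind at that site, or a coin toss when the arms are level. For a known block of 4:

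- 1st allocation: 1/2 correct.
- 2nd: 2/3, because two of the three remaining places belong to the other arm.
- 3rd: the first two match with probability 1/3, and the rest is then certain; otherwise it is a coin toss. 1/3 × 1 + 2/3 × 1/2 = 2/3.
- 4th: always certain, 1.

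Share correct = (0.500 + 0.667 + 0.667 + 1) / 4 = 0.708. Share certain = (1/3 + 1) / 4 = 0.333. The same recursion gives the other fixed sizes. The varied schemes were simulated over 88 allocations.

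| Assumed scheme | Correct guesses | Certain allocations |
|---|---|---|
| No information | 50% | 0% |
| Fixed 2, known | 75.0% | 50.0% |
| Fixed 4, known | 70.8% | 33.3% |
| Fixed 6, known | 68.3% | 25.0% |
| Fixed 8, known | 66.6% | 20.0% |
| Varied 2/4/6 | 69.6% | 3.9% |
| Varied 4/6 | 68.6% | 5.9% |
| Varied 4/6/8 | 67.3% | 2.4% |

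In the varied rows, the guess rate is for someone who does not know the sizes. The certain share is for someone who knows the set of possible sizes. Simulating the fixed sizes over 29, 29 and 30 participants, where the last block may be cut short, gives slightly lower guess rates: 74.4%, 70.1%, 67.6% and 65.2% for sizes 2, 4, 6 and 8.

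**Reading.** Varying the block size removes most of the certainty (2–6% instead of 20–50%) but hardly touches the guess rate (67–70% instead of 67–75%). What matters is whether the person who holds the history also recruits.

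**Scale for attendance.** In an arm of 44, replacing one person who would miss the four-session mark by one who would reach it moves the rate by 1/44 = 2.3 percentage points. How often that would happen cannot be derived from the document.

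**The case against.** The strongest defence is that concealment is already sound. The sequence sits in a third-party service set up by a statistician with no later role, and the arm appears only after consent, eligibility and baseline. Consent is shared by four people. The research assistant administers the PHQ-9, and two psychiatrists assess it with the health history. They are also listed recruiters, but nothing says they see allocations. The mixed model adjusts for site and the baseline score, so selection on measured severity is at least partly dealt with. The 80% retention criterion at T1 is set for the trial as a whole, so steering a person to one arm or the other does not directly distort it. The trial tests no hypothesis. The guess rates describe permuted blocks in general, and nothing converts them into a bias in PHQ-9 points.

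Most of that stands, and it rules out a stronger reading. A reader might infer that upcoming allocations can be foretold. The document does not support this: common certainty needs fixed block sizes known to the randomiser, and the article neither says nor implies either. Nor is silence about block size a defect, since a protocol article may leave it to the full document or withhold it to protect concealment.

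The defence does not reach selection on motivation. Keenness is not a baseline covariate in the outcome model, and central allocation does not erase the history that one consent-taker holds.

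**Conclusion.** The point holds as a weakness in how roles are assigned. One person randomises, sees each arm immediately and is on the consent team, and can therefore guess the next arm correctly about 67–75% of the time instead of 50%. This assumes that the matching initials denote one person, that the person attends to the history, and that the block schemes are among those tabulated; incomplete last blocks can lower the rate to about 65%.

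The consequence is moderate and unquantified: possible selection on motivation, affecting the PHQ-9 interval and the attendance criterion. The text gives no ground for inferring that selective enrolment took place, or that overall retention at T1 would be biased. The change is still worth making because it costs almost nothing, and selection at entry on an unmeasured trait cannot be put right in the analysis.

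**What to change.** State in the Procedure section that whoever submits the randomisation form takes no part in consent or eligibility decisions, that the three other listed recruiters handle these, and that allocation histories are not shared with them while recruitment continues. The existing order, with eligibility and baseline before randomisation, can stay as it is.

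Trial status gives 6 September 2022 as the planned end of recruitment. If recruitment has closed, report for the participants who took consent and who randomised, and separate the two roles in the definitive trial.

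The cost is a reassignment of tasks among existing staff, with slight scheduling inconvenience. It needs no change to the sample size, the sequence or the analysis.

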#### Usual care protocol

The usual care only arm will act as the control. They will be treated in accordance with the current NHS care by their medical providers. During the study, they may be taking medications, be on waiting lists for engaging in talking therapies, or participating in other social prescribing activities. Their participation in other interventions will be variable and we will ask them to record any treatments or interventions they engage in. Participants randomised to this group will be given the opportunity to participate in an introductory course of outdoor swimming upon completion of the study to thank them for their participation. This was advised by PPI representatives as a way to increase the likelihood of participants agreeing to the randomisation process and reduce the number who may drop out. Funding for these courses has been secured.

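### At telephone assessments the resource-use form is likely to disclose the arm to the blinded research assistant, and the stated safeguards do not cover this

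*Protocol article*

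**What the plan says.** All references are to the protocol article.

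- **Blinding.** Under Procedure, participants may choose to "complete the T1 and T2 measures with an RA present by telephone (who will be blind to group allocation"). The same section adds: "The RA-supporting participants to complete measures will remain blinded until all quantitative data is collected".
- **Telephone mode.** The Potential mechanisms section lists "surveys completed by phone with the participant" as one of three ways to complete the surveys, beside online and paper.
- **Battery.** Under Health economic measures: "The following health economics outcomes and measures will be collected at T0, T1 and T2". These include the modified CSRI, which is to "collect information on participants’ type and intensity of usual care for depression for the duration of the study" and also covers "use of other health and social care resources (e.g. GP visits, medications) and time/cost of travelling to/from treatment locations". An adapted productivity questionnaire (iPCQ) belongs to the same set. Participants also receive diaries to help them recall the resources they used.
- **Safeguards.** Under Procedure, participants are asked to keep their allocation to themselves. If an RA who has to be present becomes unblinded, another blinded team member completes the assessment.

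**The concern.** The person who is to stay blind may be on the telephone while the participant answers questions about care received and journeys to it. For someone in the swimming arm, the truthful answer to the travel item may well be the swim site. The disclosure would then come from the form itself and not from a careless remark, which is the case the safeguards are built for.

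Two things are at stake. The smaller is the scores: the PHQ-9 difference at T1 enters the decision on a full trial (Planned data analysis), and a helper who knows the arm could colour answers given by telephone. The larger is the claim of blinding. This study tests procedures for a definitive trial. A procedure that its own questionnaire defeats would be reported as working and carried forward.

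**Working it through.** The document gives no figure for unblinding, so the main check sets its statements side by side. A short calculation then bounds the effect on the PHQ-9.

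**Step 1. Is the CSRI in the telephone battery?** It is collected at T0, T1 and T2, and the telephone option applies to the T1 and T2 measures without exception. No text takes the resource-use forms out of the call.

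**Step 2. Can the answers disclose the arm?** The article describes separate logs for setting up and running the courses, with specific logs for coaches, their supervisors and link workers. It describes no separate participant record of travel to the swim. The CSRI is the only form described as asking participants about "time/cost of travelling to/from treatment locations". Under the societal perspective the article adopts, a swimmer's travel would most naturally be recorded there. Disclosure is therefore likely. It is not proven, because the form is not shown and the article does not say whether a swim site counts as a treatment location.

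**Step 3. Do the safeguards deal with it?** The request not to reveal the arm pulls against a question about treatment and travel in the same call. A substitute would put the same items to the same participant, so changing the person leaves the cause in place.

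**Step 4. What depends on order and on who takes the form?**

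| CSRI at T1 and T2 | Scales in that call | Stated RA blinding |
|---|---|---|
| Before the scales, with the RA | exposed | likely lost |
| After the scales, with the RA | protected at T1; at T2 only if another RA takes over | likely lost at the end of T1 |
| Last, self-completed or with someone else | protected | can hold |

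Order alone protects the T1 scales. Keeping the RA blind to the end of data collection also needs the form taken away from the RA.

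**Step 5. Size.**

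- Planned sample, from Design and sample size: 35 per arm and 20% drop-out. 35 / (1 − 0.20) = 43.75, rounded up to 44 per arm; 2 × 44 = 88, the stated total.
- Assumptions: a share p of swimmers uses the telephone (25%, range 10% to 50%), and an unblinded RA lowers their PHQ-9 by 1 point, with no effect in controls.
- Swimmers affected: 35 × p = 8.75 (3.5 to 17.5), so about 9 (4 to 18).
- Shift in the mean difference: p × 1 = 0.25 (0.10 to 0.50) points.
- Against the 1.7-point threshold: 0.25 / 1.7 = 15% (0.10 / 1.7 = 6%; 0.50 / 1.7 = 29%).
- Unadjusted 95% half-width at 35 per arm, with an assumed SD of 4 to 6: 1.96 × SD × √(2/35) = 1.9 to 2.8 points.

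The shift also supposes that every telephone swimmer discloses the arm before the PHQ-9 is finished, so for a 1-point effect it is an upper figure. The progression rule asks whether the interval includes 1.7. A shift of 0.25 could alter the answer only if an interval limit lay within 0.25 of 1.7.

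**The case against.** The case on the other side is substantial, and most of it limits the point.

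- **The protocol foresees unblinding.** It has two safeguards. A reader might infer that blinding cannot hold, or that the form is bound to reveal the arm. The document does not support that: the CSRI is described mainly in terms of usual care and health and social care use, and its wording is not shown. Likely is as far as the text goes.
- **T2.** A reader might infer that an RA unblinded at T1 will support the same participant at T2. The substitution rule can be read to cover T2, so this is not established.
- **The usual care record.** The statement "we will ask them to record any treatments or interventions they engage in" concerns the usual-care arm only and is not said to be part of the telephone battery. It is no evidence that swimmers would disclose their arm.
- **Order of forms.** An article may leave this to the full protocol, so its absence is no fault. The article lists the clinical measures first, then the mechanism scales, then health economics. If the survey follows that order (an assumption), the T1 PHQ-9 is finished before any CSRI item.
- **Weak route to bias.** The PHQ-9 is self-reported by participants who know their arm. The RA helps and does not rate, and telephone help is optional.

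What stands is the tension between two things the article itself fixes: an RA blind to the end of data collection, and a battery taken with that RA that is likely to disclose the arm. Neither the listed order nor the substitution rule removes it.

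**Conclusion.** The point holds in a limited form. For participants who choose telephone help at T1 or T2, the resource-use form is likely to disclose the swimming arm to an RA whom the protocol describes as blind throughout, and the stated safeguards do not address disclosure that the form itself prompts.

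The numerical effect is probably small. The 0.1 to 0.5 points rest entirely on an assumed telephone share and an assumed 1-point effect, and such a shift would seldom change the progression decision. The conclusion does not rest on that figure. It rests on the blinding statement, which may be reported without having been achieved. The inference assumes that swimmers' journeys are recorded on the CSRI; if the form excludes them, the risk is much lower. This is an inexpensive improvement to make, not a flaw that undermines the trial.

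**What to change.** For telephone completers at T1 and T2:

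1. Complete and lock the PHQ-9, GAD-7, short WEMWBS and the mechanism scales first. The two quality-of-life measures can join this block, since as described they do not ask about services used.
2. Take the CSRI and iPCQ last, either self-completed (online or on paper) or with an existing team member who is not the outcome RA.
3. Record the mode of completion for each assessment and every unblinding event, with its time point, and report both by arm, so that the results state how far blinding held.
4. Say in the Procedure section that the RA's blinding covers the scales in item 1 and that the resource-use forms are taken separately.

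The cost is a reordered survey and two additional fields, with no additional staff. The drawback is that a few telephone completers finish one form alone or speak to two people, which may cost some completeness on the resource-use forms. The mode log would show whether it does.
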